| **Title:** | *Getting Malaria “off the backs” of women and children in western Uganda* |
| --- | --- |
| **Précis:** | The study is a double-blind, randomized placbo-controlled trial of permethrin-treated *lesus* to prevent *P. falciparum* malaria in children 6–24 months of age conducted at two sites in rural western Uganda. Participating mother-infant pairs will receive a new LLIN and two permethrin-treated or untreated *lesus* at enrollment. We will follow participants longitudinally for 6 months. Participants will present to one of the two study clinics when a fever develops, where they will be evaluated, tested, and treated, if positive, for malaria. Participants will also attend scheduled clinic visits every 2 weeks for routine surveillance of adverse effects and to test for asymptomatic infection. Re-treatment and sham re-treatment of *lesus* will occur each month. |
| **Objectives:** | The scientific objective is to demonstrate the protective effect of permethrin-treated *lesus* against *P. falciparum* malaria in infants and young children. |
|  | **Primary Outcome**: Incidence of clinical, RDT-confirmed *P. falciparum* malaria in children |
|  | **Secondary Outcome(s)**: Change in child’s hemoglobin and growth parameters |
| **Population:** | The general population of mothers and children (6–18 months of age at enrollment) residing in a malaria-endemic, rural area of western Uganda. The total sample size will be 400 mother-infant pairs with 200 pairs in each arm. |
| **Phase:** | N/A |
| **Number of Sites:** | 1. Bugoye Level III Health Center  2. Mukathi Level III Health Center |
| **Description of Intervention:** | Permethrin-treated cloth used to carry infants and young children on a mother’s back (aka “lesu”) |
| **Study Duration:** | 36 Months |
| **Subject Participation:** | 6 Months |
| **Time to Complete Enrollment:** | 12 Months |

**PROTOCOL SCHEMA**

[figure not shown]

# INTRODUCTION: BACKGROUND INFORMATION AND SCIENTIFIC RATIONALE

## Background Information

Over the past two decades, the burden of *Plasmodium falciparum* malaria has substantially declined, with mortality in SSA decreasing by more than 35% [1]. However, current interventions, including long-lasting insecticidal nets (LLIN) and indoor residual spraying (IRS), are insufficient to drive vectorial capacity below the critical thresholds needed to interrupt transmission [2, 3]. In addition, these household-based interventions can drive a dynamic set of ecological and evolutionary responses to selection pressure [4]. For example, LLINs and IRS will favor *Anopheles* mosquito species and feeding behaviors that avoid contact with the interventions, either by feeding on peri-domestic animals, outdoors, or in the early evening when residents are outside the home and household-based measures offer little protection [5-8].

As evidence of these challenges, the last three *World Malaria Reports* published by the World Health Organization (WHO) suggest that progress against malaria has stalled and may even be slipping backwards in high-burden countries, particularly those in SSA [9]. Uganda has one of the highest burdens of malaria, representing 5% of cases and 3% of deaths globally [9, 10]. Despite progress, malaria still accounts for approximately 20% of outpatient visits and inpatient admissions [11]. Uganda has observed widespread rise in the prevalence of mosquitoes that are resistant to the first-line insecticides used in LLIN and IRS programs [12, 13]. Furthermore, there is emerging evidence that local malaria vectors, primarily *Anopheles gambiae* and *A.* *funestus* are increasingly exhibiting feeding behaviors that may not bring them into contact with existing interventions [14]. Thus, further innovations in malaria control are urgently needed [15-18].

[figure not shown]
In pursuit of this goal, we sought to leverage the traditional practice of mothers carrying young children on their backs utilizing wraps made from locally purchased cloth (**Figure 1**). The wrap, called a *lesu* in Uganda, also serves as a blanket or swaddle for children when they are put down or put to bed. Thus, mother and child spend much of the day in contact with the cloth. We hypothesized that when treated with an insecticide or repellent, the *lesu* might provide an additional layer of protection against malaria. A similar intervention has been shown effective for preventing mosquito and tick bites among outdoor workers in the Southeastern United States [19, 20]. Our approach has many potential advantages including: (i) targeting the most vulnerable (i.e. young children), (ii) integrating with existing cultural norms, and (iii) complementing current prevention strategies by offering protection against outdoor- and/or day-time biting *Anopheles* mosquitoes.

**Figure 1:** Ugandan mother carrying her child in a *lesu*.

## Pilot Study

As the first step towards testing this hypothesis, we conducted a pilot randomized controlled trial (RCT) of permethrin-treated *lesus* (NCT04102592) to assess safety (i.e., skin reactions, nausea), acceptability, and feasibility before proposing a larger clinical trial. Leveraging the existing network of village-based community health workers, we enrolled 50 mother-infant pairs from four villages neighboring the Bugoye Level III Health Center, our primary clinical site in rural western Uganda. Study staff conducted baseline home visits to document demographic and household characteristics, including malaria knowledge and care-seeking behaviors using a modified questionnaire from the most recent *Uganda Demographic and Health Survey* [21]. Upon completion of the survey, all participants received a new LLIN with guidance that the net was intended for the child.

[figure not shown]

Participating mother-infant pairs were randomized to either permethrin-treated (intervention) or untreated (control) *lesus*. The *lesus* of participants in the intervention group were treated and subsequently retreated each month with 0.5% permethrin (Sawyer Products, Safety Harbor, FL). The *lesus* of participants in the control group underwent sham treatment and re-treatment in which the cloth was soaked in water for a period of time similar to that of the intervention group. Participants and clinical staff but not administrative staff were blinded to group assignments.

**Table 1:** Summary of demographic and clinical variables among pilot study participants stratified by intervention group.

Every two weeks, participants attended study visits where clinical staff assessed mothers and infants for adverse reactions and performed testing for malaria using a malaria RDT. Research staff administered a brief questionnaire of recent medical history (e.g., rash, fever), care-seeking, and frequency of *lesu* use and washing. We also measured the child’s mid-upper arm circumference (MUAC), a validated tool for assessing nutritional status [22] and Hb levels at the initial and 12-week visits. At study completion, participating mothers completed a semi-structured interview eliciting perceptions of safety and effectiveness. Study procedures were approved by the University of North Carolina Institutional Review Board (18-1819), the Mbarara University of Science and Technology Research Ethics Committee (05/08-18), and the Uganda National Council of Science and Technology (SS 4833).

A total of 48 of 50 mother-infant pairs completed study activities. Two participants only completed baseline activities and replacements were subsequently recruited bringing the total to 50 participants. Overall, caregivers had relatively low educational attainment, multiple children in the home, and limited resources, although these characteristics were generally well-balanced between the groups. Almost all mothers reported using the *lesu* to carry the child on their back, while about one-third (n=17, 34%) also reported using the *lesu* as a blanket to put the child down to sleep.

At the conclusion of the 12-week follow-up period, only one adverse event - a transient, mild rash - was reported in a child in the intervention group. This rash was not confirmed at the time of physical examination. No side effects were reported by mothers. Mothers in the intervention group did report washing *lesus* more frequently compared to those in the control group (4.7 vs 3.5 times per 2-week period). Rates of care-seeking (28 visits vs. 27 visits), malaria RDT positivity at any visit (8.4% vs. 10.7%), malaria treatment (6 events vs 5 events), and changes in Hb (0.78 g/dL vs. 0.87 g/dL) were not significantly different between the intervention and control group, respectively, although the study was not powered to detect differences. We did observe a greater change in MUAC between baseline and final visit (0.57 cm vs. -0.14 cm) among children in the intervention group. There was no difference in reported level of satisfaction with the *lesu* between intervention and control groups as evidenced by questions assessing willingness to recommend and willingness to pay extra for a treated *lesu*.

## Rationale

### Intervention

Permethrin is a synthetic insecticide with a well-established safety record, being utilized to treat LLINs, military uniforms, and other clothing [23-25]. The CDC recommends the treatment of clothing with permethrin to prevent mosquito bites in all populations, and specifically reiterated this guidance for pregnant women traveling to Zika-endemic areas to reduce the risk of infection [26]. Notably, permethrin also has a modest repellent effect, which may prevent biting even when mosquitoes are resistant to the killing effect [27].

The *lesus* of participants in the intervention group will be treated and subsequently retreated each month with 0.5% permethrin (Sawyer Products, Safety Harbor, FL) – the same concentration approved by the U.S. Environmental Protection Agency (EPA) and used in military and civilian applications. While the frequency of retreatment was greater than that used with early studies of insecticide-treated nets, our concern is that washing, especially if *lesus* were frequently soiled and washed using traditional methods, might cause premature washout of the permethrin. This has been reported in previous studies of permethrin-treated school uniforms when used to prevent dengue infection [28]. Instead, our intent is to (i) test for potential adverse effects associated with persistent contact at optimal concentrations and (ii) minimize any differences in the preliminary efficacy aims due to washout.

###
[figure not shown]
Study Site & Population

The study will take place in the Bugoye and Malaiba sub-counties located in the Kasese District of western Uganda (**Figure 2**). The two sub-counties have populations of 50,249 and 47,769 respectively, with approximately one-fifth of the population being children less than five years of age [29]. Subsistence farming (e.g. cassava, sweet potatoes, maize) represents the primary economic activity, although a high proportion of households also keep livestock, including chickens (88%), goats (74%), and cattle (14%) in the peri-domestic space [30]. The vast majority of residents do not have access to water or electricity in the house, and one-third of households live ≥5 km to the nearest public health facility [29]. This population is generally representative of rural populations throughout malaria-endemic East Africa.

**Figure 2:** Maps showing the location and topography of the proposed study areas. From Mirembe et al, *Plos One* 2017.

The climate in Bugoye permits year-round malaria transmission marked by semi-annual transmission peaks typically following the end of the rainy seasons in May and December [31]. The most recent malaria indicator surveys undertaken in the mid-western region (2014-15) and Tooro sub-national region (2018-19) which include the study area, reported *P. falciparum* parasitemia rates (PfPR) of 17.4% and 7.3%, respectively [32, 33]. However, in a recent cross-sectional survey of more than 2,100 households in the Bugoye Sub-County, we found that the PfPR among children 2 to 8 years of age was upwards of 30% in many of the low-elevation villages. We will recruit and enroll participants from these high transmission villages located along the river basins. The duration of study participation for each mother-child pair is 6 months, which is intended to capture one dry and one wet season.

## Potential Risks and Benefits

### Potential Risks

- **Skin Irritation** – Participants in the intervention group, especially young children, may develop dermatitis or allergic reactions resulting from direct contact with the permethrin. Only one such episode was reported in the pilot study, which was mild and resolved prior to clinical evaluation.
- **Phlebotomy** – Participants may experience discomfort when blood is drawn. There is also a very small risk of bruising and/or infection associated with the blood draws.
- **Loss of Privacy** – There is also the risk of loss of privacy and/or confidentiality concerning medical history and test results should any study documents be compromised or lost.
- **Change in Behavior** – Participating mothers may alter usual activities intended to prevent mosquito bites (e.g., LLIN use, repellents, long-sleeved clothing) assuming that they are protected by the *lesu*.

### Potential Benefits

- **New LLINs, *Lesus*, and Personal Protective Equipment (PPE)** – Participants will receive new LLINs to ensure that mother and child have access to coverage in the home, along with two *lesus* for carrying the child, and PPE (e.g., facemasks, sanitizer) to reduce the spread of COVID-19 during study activities. Participants will keep the LLINs and *lesus* upon completion of the study.
- **Reduced risk of malaria** – Participants in the intervention group may receive an additional level of protection against malaria and other vector-borne diseases as a result of utilizing the treated-*lesu*.
- **Prioritized Case Management** – Participants in both groups will have expedited, no-cost access to the study clinics for evaluation and treatment. The study will ensure there are no stockouts of diagnostics (e.g., RDTs) or anti-malarial treatments.
- **Knowledge Generation** – Participants will be contributing to the evaluation of a novel intervention that, if effective, may help reduce the incidence of malaria not only in the local community, but across SSA.

# OBJECTIVES

## Study Objectives

The overarching goal of this proposed project is to expand the malaria “toolbox” with a scalable, low-tech, low-cost intervention that leverages existing cultural practices and established insecticides to reduce the burden of *P. falciparum* malaria among young children in SSA. Our scientific objective is to demonstrate the protective effect of permethrin-treated *lesus* against *P. falciparum* malaria in infants and young children. To test this hypothesis, we propose to:

**AIM 1: Determine the effectiveness of permethrin-treated *lesus* to prevent *P. falciparum* malaria infection among infants and young children (6–18 months of age).** We will conduct a randomized controlled trial of 400 women-infant pairs at two sites in rural western Uganda leveraging methods similar to those employed in our pilot study. In brief, all participants will be followed longitudinally to capture incident febrile illness, even when occurring between scheduled visits. Our primary outcome is clinical malaria, defined as the presence of typical symptoms (e.g., fever, lethargy) and a positive malaria RDT during observation. Specifically, we hypothesize that the intervention will reduce malaria cases among infants and young children by at least 30% relative to children receiving untreated *lesus*.

**AIM 2: Explore the effectiveness of permethrin-treated versus untreated *lesus* to prevent *P. falciparum* malaria infection among mothers.** Using the same methods outlined in Aim 1, we will assess potential reductions in malaria incidence among mothers as an additional benefit of *lesu* use. If the permethrin-treated *lesu* is effective, it could provide preliminary evidence to support the use of insecticide-treated clothing as a complementary strategy to prevent malaria in pregnancy. We hypothesize that the intervention will have a modest impact, defined by at least a 10% relative reduction, in malaria parasitemia, either symptomatic or asymptomatic, among mothers.

## Study Outcome Measures

| **Study Measure** | **Method of Collection** |
| --- | --- |
| 1. Primary Outcome |  |
| 1.A. Incidence of clinical malaria in child | (1) Acute febrile illness AND positive RDT at scheduled or unscheduled study clinic visit  - or -  (2) Written documentation of fever AND positive RDT from non-study clinic visit |
| 2. Secondary Outcomes |  |
| 2.A. Change in child’s Hb level | Hb measured at baseline (Week 0), Week 12, and Week 24 visits using HemoCue® device. |
| 2.B. Change in child’s growth measures | Height, weight, measured at baseline (Week 0), Week 12, and Week 24 visits. |
| 2.C. Change in child’s nutritional status | MUAC measured at baseline (Week 0), Week 12, and Week 24 visits [22]. |
| 2.D. Asymptomatic parasitemia in children | Presence of malaria parasites on bi-weekly dried DBS as determined by qPCR. |
| 2.E. Hospitalization for malaria | Self-reported history of hospitalization on bi-weekly questionnaire AND confirmation by study staff. |
| 2.F. Clinical malaria in mother | Same as 1.A. |
| 2.G. Change in mother’s Hb level | Same as 2.A. |
| 2.H. Burden of care-seeking | Self-reported history of clinic visits, work days missed, health expenditures on bi-weekly questionnaires. |
| 3. Safety Measures |  |
| 3.A. Adverse reaction to treated-*lesu* | Self-reported history on bi-weekly questionnaire and confirmation by clinical staff. |
| 3.B. Severe adverse event (SAE) | Care-seeking, hospitalization, or death attributable to the intervention. |
| 4. Covariates of Interest |  |
| 4.A. Socioeconomic status | Questions from baseline survey on ownership of mobile phone, vehicle, etc. [34] |
| 4.B. Maternal education | Self-reported history on baseline questionnaire. |
| 4.C. Frequency of *lesu* use and washing | Self-reported history on bi-weekly questionnaire, use diaries, direct observation. |
| 4.D. Residual permethrin levels | Punches of *lesu* cloth taken at 2-, 4-, 6-month visits tested by gas chromatography [35] |
| 4.E. *Anopheles* mosquito density | CDC light trap collections in peri-domestic space (indoor/outdoor) with species identification |

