## Bi-Monthly Visits (Days 14, 28, 42, 56, 70, 84, 98, 112, 126, 140, 154)

Participants will be scheduled in advance for a follow-up visit at the same health center every 2 weeks. Activities at each visit include:

- Confirm participant identify and study number.
- Administer questionnaire reviewing changes in medical history since the last visit.
- Record adverse events as reported by subject or observed by investigator.
- Measure and record vital signs, including:
  - Child’s height, weight and MUAC
  - Child’s axillary temperature
- Draw 50 µL capillary blood by finger-prick or heel stick from the child to create DBS for qPCR testing at a later date.
- Provide an in-kind incentive (e.g., sugar, soap, cooking oil) and travel supplement, the combined value of which is estimated to be approximately $4–5 per visit.
- Provide a card to remind them of the date and time of their next visit.

The following visits will have additional activities:

- **Visits on Day 28, 56, 70, 98, 126, 154**: Retreatment of *lesus*
- **Visits on Day 56 and 98**: Punch from *lesus* to measure permethrin content
- **Visit on Day 84**: Venous blood draws (mother/child) instead of capillary to:
  - Perform testing for Hb concentration
  - Create DBS for qPCR testing at a later date.
  - Store sera for future seroprevalence studies of vector-borne disease

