### Physical examinations

Study staff will measure vital signs including height, weight, MUAC, and axillary temperature at each visit. A clinical officer will perform a general physical examination, including full inspection of the skin, of all participating children at the baseline visit. At subsequent visits, a clinical officer will be available to perform focused clinical assessments, but only in response to adverse events reported by participants or staff.

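### Read literally, safety outcome 3.A counts only clinician-confirmed reactions; this is narrower than the protocol's own adverse-event recording and would leave out the one reaction reported in the pilot

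*Protocol*

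**What the plan says.** Protocol Section 2.2, Study Outcome Measures, gives the method of collection for outcome 3.A (adverse reaction to the treated lesu) as "Self-reported history on bi-weekly questionnaire and confirmation by clinical staff".

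The Pilot Study section says that "only one adverse event - a transient, mild rash - was reported in a child in the intervention group", and adds: "This rash was not confirmed at the time of physical examination". Section 1.4.1, Potential Risks, lists skin irritation first and describes the same pilot episode as one "which was mild and resolved prior to clinical evaluation".

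On examination after baseline, Section 7.1.3 makes a clinical officer available for focused assessments, "but only in response to adverse events reported by participants or staff". Appendix A2 marks a physical examination for the child only at baseline and at unscheduled acute visits. On visit spacing, Section 6.4 states: "Participants will be scheduled in advance for a follow-up visit at the same health center every 2 weeks".

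Other sections record events more widely. Sections 6.4 and 6.5 have staff record adverse events that the participant reports or the investigator observes. The table in Section 8.1 puts any rash or skin lesion in the database and requires the principal investigator to be told. Section 8.1.2 defines an adverse event without asking for confirmation. Section 10.3.2 then plans a descriptive summary by arm of two safety measures: adverse reactions to the treated lesu, and serious adverse events.

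**The concern.** Skin irritation is the one listed risk that comes from the product itself, and the only example the protocol gives was mild and short. An outcome that requires a clinician to confirm the reaction, with scheduled contacts two weeks apart, is poorly suited to short reactions. The document also holds two standards: a wide one for recording events and a narrow one for the named outcome. It never says how a reported but unconfirmed reaction is classified.

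What is at stake is the published safety result. If 3.A is applied as written, the reaction rate by arm could come out lower than the trial's own records support. This trial puts insecticide on cloth in prolonged contact with infants, and the Rationale section gives detection of adverse effects from persistent contact as one reason for monthly re-treatment.

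**Working it through.** No sample size, power or alpha figure depends on 3.A. The protocol's own figure here is the pilot count: 1 reaction reported, 0 confirmed.

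**1. Is 3.A conjunctive?** Within the Section 2.2 table, alternatives are marked with an explicit 'or' (1.A), several sources are listed with commas (4.C), and outcomes resting on self-report alone say so (2.H, 4.B). Row 3.A joins self-report and confirmation with 'and', the same structure as 2.E. The literal reading is that both are needed.

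**2. What does confirmation mean?** The row does not define it. The only other place the protocol speaks of a reaction being confirmed is the pilot account, where the word is tied to physical examination.

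**3. Apply 3.A to the pilot.** Reported: 1. Confirmed: 0. The literal rule counts 0 of 1. The pilot's arm sizes cannot be read from the text. Taking 25 per arm from 50 pairs as an assumption, with one-sided 95% Clopper-Pearson upper limits:
- all reports: 1/25 = 4.0%, upper limit 17.6%;
- confirmed only: 0/25 = 0%, upper limit 1 − 0.05^(1/25) = 11.3%.

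Over 23 to 27 per arm, the limits run from 19.0% down to 16.4% (one event) and from 12.2% down to 10.5% (none).

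**4. Follow a transient reaction through this trial.** A rash starts and clears between two visits. The mother reports it at the next visit, so it is recorded under Section 6.4. The officer examines and finds nothing. It is an adverse event under Section 8.1.2 but fails the literal 3.A. Section 10.3.2 names no other safety summary by arm in which it would appear.

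**5. How often could that happen? An illustration only.** Assume onset is uniform over the 14-day interval, examination happens only at the scheduled visit, and a rash lasts d days. None of this is in the document. The chance that the rash is still visible is d/14. The last column applies it to an assumed 4% true rate, which is 0.04 × 200 = 8 children in an arm of 200.

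| d (days) | d/14 | Confirmed of 8 |
| --- | --- | --- |
| 1 | 0.07 | 0.6 |
| 3 | 0.21 | 1.7 |
| 5 | 0.36 | 2.9 |
| 7 | 0.50 | 4.0 |

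Earlier unscheduled examination would raise every value.

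**6. Effect on the comparison.** Let q be the probability that a reported reaction is confirmed, equal in both arms, and let r1 and r0 be the true reaction rates. The recorded rates are q·r1 and q·r0. Their ratio is still r1/r0. Their difference is q(r1 − r0), smaller than r1 − r0 whenever q is below 1. The rule therefore lowers absolute rates and the absolute difference, and leaves the relative comparison unchanged in expectation.

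**The case against.** The strongest reply is that 3.A is loose wording, not an exclusion rule. It stands in a column on how data are collected. Its 'and' is lower case, whereas 1.A and 2.E use capitals where both conditions bind. Confirmation could mean a clinician's judgement of relatedness (Section 8.3.1) and not a visible sign. The pilot, whose methods Aim 1 says this trial follows, did report its unconfirmed rash as an adverse event, by arm. All this is possible, and it is why the point is stated as a literal reading. But the row does not say it, and the pilot text uses 'confirmed' for a finding on examination. If pilot practice is intended, 3.A should say so.

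Second, nothing is lost to oversight. Reported events are recorded at every follow-up visit, any rash goes to the principal investigator, the monitoring board sees data separated by arm (Section 9), and the halting rule (Section 8.5) works on graded events and not on 3.A. This stands. The gap is in the named outcome and its summary, not in the trial data.

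Third, a reader might infer that the rule strips events mainly from the permethrin arm and so biases the comparison in its favour. The document does not support that. The rule is the same in both arms, clinical providers are blinded (Section 4.4.2), and nothing indicates a different chance of confirmation by arm. More events could be dropped where more arise, but that is proportional loss.

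Fourth, how unconfirmed reports are tabulated could be left to the statistical analysis plan. Layout could be; the outcome definition is fixed in the protocol.

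**Conclusion.** The point holds as an inconsistency with a practical consequence. Read literally, 3.A is narrower than Sections 6.4, 6.5, 8.1 and 8.1.2. It would not count the only reaction the pilot reported, and it could leave transient reactions out of the safety summary that Section 10.3.2 names, although they are in the database. The direction is a lower absolute reaction rate and possibly a smaller absolute difference between arms.

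The size cannot be derived from the document. A reader might take the complement of the illustrative probabilities, 1 − 0.36 = 64% to 1 − 0.07 = 93% for rashes of five days down to one, as an expected undercount. It is not one: the durations, uniform onset and absence of earlier visits are all assumed. Participants have free, expedited clinic access (Section 1.4.2), although Section 6.6 directs unscheduled visits to fever and malaria-like symptoms and does not mention rash. The pilot's 4% rests on a single event and an assumed arm size.

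The safety analysis is descriptive, so no test or error rate is affected. The change is worth making because it costs little and affects what is reported.

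**What to change.** Reconcile 3.A with Sections 6.4, 6.5, 8.1 and 8.1.2:

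- In Section 2.2, define 3.A as any adverse reaction reported by the mother or observed by staff.
- On the case report form, record confirmation status as an attribute of each reaction: confirmed, resolved before examination, or refuted on examination.
- In Section 10.3.2, tabulate all reported or observed reactions by arm, with the clinician-confirmed subset beside them.

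The cost is one row of wording, one form field and one extra line in a table; the reports themselves are already collected at each visit. The downside is that some non-specific rashes will be counted in both arms. The sham-treated control arm shows that background rate, and the confirmed subset keeps the more specific count in view.
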